### Relevant concomitant care permitted or prohibited during the trial {11d}

For ethical reasons, all types of care as usual are permitted during the trial. Parents are asked at all assessment points if the siblings have received professional support or used support sources. Examples of care as usual could be no care, using support sources such as books, receiving help from a social worker, or attending a sibling activity, such as a fun sibling get-together or a group training.

### Provisions for post-trial care {30}

There will be no post-trial care. No harm of participation in the trial is expected. Siblings can play the serious game again for unlimited time after the study has finished. The information brochure that parents receive also includes tips for other sibling support sources.

### Outcomes {12}

A number of standardized measures complemented with a few self-constructed questionnaires are used. Parents are asked to complete the same questionnaires and open-ended questions at three measurement points. The questionnaire about demographic variables will only be completed at pre-test assessment. Siblings are also asked to complete the same questionnaires, a drawing assessment, and open-ended questions at three measurement points. The social validity scale will only be completed by the parents and siblings at pre-test by the total group and also at post-test by the intervention group. An overview of the assessments at each measurement point can be found in Table 2.

**Table 2 Tab2:** Overview of enrolment, interventions and assessments

	**Enrolment**	**Allocation**	**Post-allocation**		**Close-out**
**Timepoint**	*t*0		*t*1	*t*2	
Enrolment					
Eligibility screen	X				
Registration	X				
Informed consent	X				
Allocation		X			
Interventions					
Intervention group		X			
Waitlist control group					X
Assessments					
Demographic variables* (parent)*	X				
Control variables *(parent)*			X	X	
Quality of life *(parent and child)*	X		X	X	
Sibling adjustment to the disability of the brother or sister* (parent and child)*	X		X	X	
Self-esteem *(child)*	X		X	X	
Perceived social support *(child)*	X		X	X	
Sibling relationship *(parent and child)*	X		X	X	
Coping skills *(child)*	X		X	X	
Parent-child relationship *(parent)*	X		X	X	
Social validity *(parent and child)*	X		X		
Subjective evaluation *(parent and child)*			X		
Parenting self-efficacy *(parent)*	X		X	X	
Child behavior *(parent)*	X		X	X	

### Demographic and control variables

#### Demographic variables

The parent is asked at pre-test assessment to fill out a questionnaire about demographic variables, which is based on standard demographics and variables that were found to be important in sibling studies. The variables are (1) country (the Netherlands or Belgium), (2) gender parent that participates in the study (hereafter: parent 1), (3) relationship to child parent 1, (4) age of the parent, (5) gender other parent (hereafter: parent 2), (6) relationship to child parent 2, (7) relationship to other parent, (8) family composition, (9) work status parent 1, (10) work status parent 2, (11) education level parent 1, (12) education level parent 2, (13) household income, (14) ability to make ends meet with their household income, (15) languages spoken in the household, (16) gender child with disability, (17) age child with disability, (18) type of disability of the child, (19) comorbid disabilities of the child, (20) level of ID of the child with a disability, (21) level of VI of the child with a disability, (22) daytime activities of the child with a disability, (23) type of external care for the child with a disability, (24) nights per month that the child with a disability stays somewhere else, (25) gender sibling, (26) age sibling, (27) older or younger sibling, (28) days sibling is cared for by someone else, (29) used sibling support, and (30) used other support sibling.

#### Control variables

In addition to the demographic variables, several control variables will be included in the parent-report questionnaire at post-test and follow-up assessments in order to monitor stressful events and the utilized care as usual. Four questions can be answered: (1) changes in care or stressful events experienced by the child with a disability, (2) used sibling support, (3) used other support by the sibling, and (4) stressful events experienced by the sibling. Parents can choose between listed support sources, or name something else, and are asked to describe the experienced stressful events.

### Primary outcomes

#### Quality of life

The Pediatric Quality of Life Inventory (PedsQL 4.0) [37] is a measure of four aspects of health-related quality of life included in the subscales: Physical Functioning, Emotional Functioning, Social Functioning and School Functioning. The questionnaire will be filled out by both the parent and the sibling. Different versions are used for children aged 5–7 years and children aged 8–12 years. In this study, the Dutch version [38] of the Psychosocial Health Summary Score will be used. Specifically, the Acute version, which is filled out over the past week, will be used. The used scale has three 5-item subscales: Emotional Functioning, Social Functioning, and School Functioning. The subscale Physical Functioning is excluded, because this subscale is irrelevant for the current study. On the parent-report version and the child-report version for children aged 8–12 years, the items can be answered on a 5-point Likert scale (0 = never to 4 = almost always). On the child-report version for children aged 5–7 years, the items can be answered on a 3-point Likert scale (0 = not at all, 2 = sometimes, and 4 = a lot). An example of an item of the child-report version is: “Do you feel sad.” The internal consistency of the Psychosocial Health Summary Score was good with Cronbach’s alphas of 0.83 (child-report) and 0.86 (parent-report). Construct validity has also been demonstrated [39].

#### Sibling adjustment to the disability of the brother or sister

The Sibling Perception Questionnaire (SPQ; originally by Carpenter & Sahler [40] and adapted by Lobato & Kao [41]) measures the impact of the disability on the sibling and the sibling’s attitude towards the disability. The questionnaire has a total of 22 items on four subscales: Interpersonal, Intrapersonal, Fear, and Communication. The Dutch version [42] of both the parent-report version and the child-report version will be used in the current study. In this study, the word “illness” in the items will be replaced by “disability.” The items can be answered on a 4-point Likert scale (1 = never to 4 = often). An example of an item is: “I feel sad about the disability of my brother/sister.” In the main data analysis, the 18-item composite Negative Adjustment Scale, which is composed of the sum of the Interpersonal, Intrapersonal and Fear subscales, will be used, because a previous study [41] found that the separate subscales have low internal consistency. The internal consistency of the Negative Adjustment Scale was found to be acceptable to good with Cronbach’s alphas of 0.79 (child-report) and 0.74 (parent-report).

In addition, parents will be asked to provide a written answer to three open-ended questions about the adjustment of the sibling to the disability of the brother or sister. The siblings will be asked to verbally answer these three open-ended questions. Their answers will be audiotaped. When there is no consent for audio recording, the researcher will type down the answers of the sibling.

The questions for the siblings and parents are: (1) “Can you name up to five examples of what you/your child like(s) about your/their brother or sister?” (2) “Can you name up to five examples of what you/your child do(es) not like or find(s) difficult or unpleasant about having a brother or sister with a disability?,” and (3) “Can you explain what you/your child do(es) to deal with these examples?.” The children will also be asked to rate the examples named at question 1 and question 2 with smileys, indicating how much they like it or how hard or unpleasant they think it is. At post-test and follow-up assessments, the siblings will be asked to rate the examples named at pre-test assessment again and tell if they have changed how they deal with these kind of situations. They will also be allowed to name new examples. Parents will be asked to name what has changed in what their child likes or finds hard about having a brother or sister with a disability and how he/she deals with that. They can also name new examples.

### Secondary outcomes

#### Self-esteem

The Self-Perception Profile for Children (SPPC) [43] is a child-report scale that consists of six subscales. In order to limit the burden put on the siblings, only the Global Self-Worth subscale will be used in the current study. Specifically, the Dutch simplified 3-item version (SPPC-s) [44] of the subscale will be used, because this version is more appropriate for children aged 6–8 years. In this version, the items can be answered on a 4-point Likert scale, which is visualized with rectangles that increase in size when the answer category represents higher self-worth. An example of an item is: “Are you happy with whom you are?,” which can be answered with not happy, a bit happy, happy, or very happy. The internal consistency of the simplified 3-item Global Self-Worth subscale was acceptable with Cronbach’s alphas between 0.65 and 0.69 [44].

#### Perceived social support

The Social Support Scale for Children (SSSC) [45] is a child-report scale that consists of four 6-item subscales: Parent Support, Classmate Support, Teacher Support, and Close Friend Support. In the current study, the Dutch version [46] of the scale will be used. The items have a “structured alternative format.” The child first has to choose which of two “types” of kids they are alike, for example “Some kids have parents who don’t really understand them” or “Other kids have parents who really do understand them.” Then the child has to choose if that is "sort of true for me" or "really true for me". The items are scored from 1 to 4, with higher scores representing higher levels of perceived support. The internal consistency was good, with Cronbach’s alphas between 0.72 (Classmate Support Scale) and 0.81 (Close Friend Support Scale), and support for the validity of the scale was found [47].

#### Sibling relationship

Sibling relationship with the brother or sister with a disability is measured using two different measures. One that is completed by the sibling and one that is completed by the parent.

The Pictorial Assessment of Interpersonal Relationships (PAIR) [48] is an instrument that assesses the characteristics of a close relationship through drawings. In the current study, we use part of the instruction as described by Guidotti et al. [49]. Siblings will be asked to draw themselves with their brother or sister while doing something. The siblings receive an A4 paper, a pencil, and a set of crayons. They can take as much time to complete the drawing as they want. After they made the drawing they will be asked which figure represents whom and what they are doing. The drawings will be assessed by two independent investigators on six different scales: Cohesion, Distancing, Similarity, Value, Emotions, and Conflict. For each subscale, scores can be administered following a standard assessment procedure, which is elaborately described in the manual. The way of scoring differs per scale. In a study with siblings of children with autism spectrum disorder, the inter-rater reliability was good, with Cohen’s kappa larger than 0.90 [49]. Significant correlations between the subscales and total score, and support for discriminant validity were found [48].

The Parental Expectations and Perceptions of Children’s Sibling Relationships Questionnaire (PEPC-SRQ) [50] is a 27-item parent-report questionnaire that assesses the expectations and perceptions that the parent has of the sibling relationship of their children. On the original Perceptions scale, the parents rate the frequency, how problematic it is, how easy it is to improve, and how much they would like help with that, for each behavior. Because of the relevance to the research question, in the current study only the Perception scale will be used, and only the frequency of the behaviors will be rated by the parents. The questionnaire consists of three subscales: Warmth, Agonism, and Rivalry/Competition. At the end of the questionnaire, the parent is also asked to rate the overall quality of the sibling relationship of their children. The frequency of the behaviors is rated on a 5-point Likert scale (1 = never to 5 = always). The overall quality of the sibling relationship is rated on a 7-point Likert scale (1 = very poor, to 7 = extremely good). An example of an item is: “Loyalty or sticking up for one another.” The questionnaire was translated to Dutch by a team of researchers experienced with the population (e.g., LV) using the WHODAS 2.0 Translation package (version 1.0) [51]. The internal consistency of the original subscales is acceptable to good, with Cronbach’s alphas of 0.86 on Warmth, 0.73 on Agonism, and 0.76 on Rivalry/Competition. Support for construct validity was found [50].

#### Coping skills

The Coping Strategies Inventory (CSI) [52] originally is a 72-item questionnaire with eight primary scales, four secondary scales, and two tertiary scales measuring the types of coping strategies that children use. In order to lower the burden for the participating children, the 12-item adapted Dutch version [53] of the Engagement and Disengagement subscales of the questionnaire will be used in the current study. When completing the CSI, children are first asked to think of a difficult situation that happened in the past month. Four open-ended questions are asked to help the sibling to describe the situation. Then the child is asked to rate on a 4-point Linkert scale (1 = not at all to 4 = very much) how much the situation bothered him/her. Finally, the twelve main items about how the child reacted to this difficult situation can be answered on a 5-point Likert scale (1 = I never do this to 5 = I always do this). An example of an item is: “I blamed myself.” The validity and internal consistency of the original 72-item scale was good, with Cronbach’s alpha of. 90 for the Engagement scale, and of 0.89 for the Disengagement scale [52]. The 10-item version of Scholten et al. [53] had acceptable internal consistency for the Disengagement scale (*α* = 0.62), but insufficient internal consistency for the Engagement scale (Cronbach’s alpha is not reported). Therefore, we adapted it to a 12-item version in collaboration with one of the authors (AW).

#### Parent-child relationship

The Child-Parent Relationship Scale (CPRS) [54] is a 30-item (full version) or 15-item (short form: CPRS-SF) parent-report scale that measures positive and negative aspects of the parent-child relationship as experienced by the parent. The short form consists of two subscales: Conflicts and Closeness. In the current study, the positive aspects of the parent-child relationship are most relevant in answering the research question. Therefore, only the 7-item Closeness subscale of the short form will be used. This subscale was translated to Dutch by a team of researchers experienced with the population (e.g., LV) using the WHODAS 2.0 Translation package [51]. The items on the CPRS can be answered on a 5-point Likert scale (1 = definitely does not apply, 2 = not really, 3 = neutral, not sure, 4 = applies somewhat, and 5 = definitely applies). An example of an item is: “If upset, my child will seek comfort from me.” The internal consistency of the short-form Closeness subscale was acceptable [55], with Cronbach’s alphas between 0.64 (mothers) and 0.74 (fathers). The convergent and predictive validity of the short-form Closeness subscale was reported to be good [56].

#### Social validity and subjective evaluation

The Social Validity Scale (SVS) [57] originally is a 16-item scale to measure the desirability, feasibility, and perceived effectiveness of an intervention. The versions of the scale used in Damen et al. [58] and in Derks et al. [59] were adapted to fit the current intervention. Different versions are used for parents and siblings. At pre-test assessment, the questions are focused on the expectations about the game, at post-test assessment the questions are focused on the evaluation of the game. All parents and siblings will fill out the pre-test scale. Only parents and siblings in the experimental group will fill out the post-test scale. At the post-test assessment, additional open-ended evaluation questions are included. Items can be answered on a 5-point Likert scale, with answer categories adapted to the question (e.g., 1 = very bad to 5 = very good). The child-report version also shows smileys. Higher scores indicate more positive expectations or evaluations, with 3 being the neutral score.

At pre-test assessment, the parent and sibling will answer eight questions about the expected pleasantness, feasibility, and effectiveness. For example, one of the parent-report questions is: “I think my child can learn […] from playing the serious game ‘Broodles’.” At post-test assessment, the parent will be asked 17 and the child will be asked 23 open and closed questions about the pleasantness, perceived effectiveness, and feasibility of the serious game elements and worksheets. The open-ended follow-up questions give the parents and siblings the ability to explain their answers to the closed questions. The parent can type their answers in the provided open answer space. The answers of the sibling will be audiotaped. When there is no consent for audio recording, the researcher will type down the answers of the sibling. For example, a closed question for the child is: “How much have you learned from playing the game ‘Broodles’?” The follow-up open-ended questions are: “What is it that you have learned?,” “Which parts of the game or worksheets helped you with this?,” and “What did you miss?” In addition, the parent will also be asked five questions about the brochure with information and tips for parents.

A version of the SVS that was used in Damen et al. [60] showed good internal consistency for the subscales Feasibility (Cronbach’s *α* = 0.84) and Subjective effectiveness (Cronbach’s *α* = 0.86).

### Exploratory variables

#### Parenting self-efficacy

The Parenting Sense of Competence Scale (PSOC) [61] measures parenting self-esteem. The original scale consists of a total of 17 items on two subscales. In order to limit the burden of the parent, in the current study a 3-item adapted version of the PSOC will be used [62]. The items can be answered on a 5-point Likert scale (1 = not at all like me to 5 = completely like me). The included items are: “I feel confident in my role as a parent,” “Being a parent is manageable and any problems are easily solved,” and “I honestly believe I have all the skills necessary to be a good mother to my child.” In the current study, parents will be specifically asked to answer the question about their parenting concerning the sibling. The internal consistency of the 3-item scale was found to be good, with Cronbach’s alpha of 0.81 [62].

#### Child behavior

Six questions about the behavior of the child with a disability are answered by the parent. These questions include: (1) “My child that has a disability shows behavior that scares my child that participates in this research,” (2) “My child that has a disability shows behavior that makes my child that participates in this research happy,” (3) “My child that has a disability shows behavior that hurts my child that participates in this research,” (4) “My child that has a disability shows behavior that makes my child that participates in this research proud,” (5) “My child that has a disability shows behavior that bothers my child that participates in this research,” and (6) “My child that has a disability shows behavior that makes my child that participates in this research feel appreciated.” The parents can answer the questions on a 5-point Likert scale (0 = never, 1 = rarely, 2 = sometimes, 3 = usually, and 4 = always). The scores on the 3 items presenting negative behavior are summed, and the scores on the 3 items presenting positive behavior are summed as well.

### Participant timeline {13}

Families that show interest in participating in the study by contacting the researcher will receive the subject information letter through email. This consists of both an extensive information letter for the parent and a simplified summary for the sibling. The parent and sibling can then decide whether they want to participate in the study. When they indicate that they want to participate, the researcher will call the parent for a brief eligibility screening, to provide more information about the study procedure and to answer questions. After that the research assistant will contact the parent to plan the three home visits in which the assessments are completed. Parents are given the opportunity to choose if they want to fill out the questionnaire during the home visits or at another moment in the week prior to the visit. At the pre-test assessments, parents will hand over the informed consent forms to the research assistant prior to starting the assessment. After completing the pre-test assessments, the parent and sibling will be informed about the group they have been allocated to. The siblings in the experimental group will then play the serious game over a period of 4 weeks. The siblings in the waitlist control group can play the game after completing the follow-up assessment. A visualization of the study timeline can be found in Fig. 1.

**Fig. 1 Fig1:**
[figure not shown]
Flowchart of the study timeline

### Sample size {14}

Using GLIMMPSE 3.0 [63], the required sample size to conduct multivariate linear mixed models for the primary outcomes quality of life and sibling adjustment to the disability of the brother or sister is calculated. The sample size is estimated with an alpha of 0.05 and a target power of 0.80 and is based on an interaction effect hypothesis, including between (intervention) and within (measurement point) variance. Correlations between measurement points are estimated to be 0.60 (T0–T1; T1–T2) and 0.40 (T0–T2), based on previously found test-retest correlations on the PedsQL [64]. The correlation between the outcomes is estimated to be 0.30. This estimate is based on a previously found correlation between the SPQ and a measure of wellbeing and adjustment (Strengths and Difficulties Questionnaire; SDQ), as no information about the correlation between de SPQ and a measure of quality of life was available [65]. A scale factor of 1.2 for variability is inserted in the sample size calculation, in order to be more conservative.

For both quality of life and sibling adjustment to the disability of the brother or sister the child-report means and standard deviations from previous sibling studies are used [41, 66]. For the control group, no change is expected on the outcome measures. For the intervention group, change is expected gradually. The expected total change (at T2) on quality of life is based on the Minimal Clinically Important Difference [67]. The expected total change on sibling adjustment to the disability of the brother or sister is based on the measured change in a previous sibling intervention study [41]. No change in standard deviations is expected on all measurement points.

The computed sample size calculation based on the beforementioned parameters results in a required sample size of 134, with 67 participants in the intervention group and 67 participants in the waitlist control group. Based on two previous intervention studies [22, 29], a dropout rate of 15% is accounted for. The total required sample size is therefore 154. This includes 154 siblings and their 154 parents.

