**Methods:**

The intervention consists of a serious game called “Broodles” (in Dutch: “Broedels”) that helps children to recognize and deal with thoughts, feelings, and difficult situations. The game consists of eight 20-minute levels that all have the same structure with eight game elements. Each level addresses a domain of sibling quality of life and combines animations, mini-documentaries, fun mini-games, and multiple-choice questions. In addition to the game, siblings make a worksheet after playing each level. In order to support the child, the parents or caregivers receive a short brochure with information and tips. The effectiveness of the intervention will be investigated among a sample of 154 children aged 6–9 years and their parents or caregivers, using a two-arm parallel RCT design. The experimental group will play the serious game “Broodles” over a period of 4 weeks, whereas the control group will be placed on a waiting list. Assessments will take place at three time points: pre-test (week 1), post-test (week 5), and follow-up (weeks 12–14). At each timepoint, children and parents will complete several questionnaires on quality of life and different aspects of psychosocial well-being. In addition, children will make drawings to assess the sibling relationship. Next to that, parents and children will answer closed and open-ended questions about the sibling adjustment to their brother or sister’s disability. Finally, parents and children will evaluate the serious game through closed and open-ended questions.

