## Assignment of interventions: allocation

### Sequence generation {16a}

The participants will be randomly allocated (1:1) individually to the experimental and control group using an allocation schedule. The randomization will be stratified by sibling age, including two stratification groups: siblings aged 6 and 7, and siblings aged 8 and 9. Stratification by sibling age is executed because we expect that the age of the sibling can influence the intervention effect. Next to stratification, block randomization will be used in order to ensure equal group sizes. The block sizes will be randomized as well, varying between 4, 6, and 8.

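### The enrolment target of 154 allows for about 13% dropout, not the stated 15%, because 134 was multiplied by 1.15 rather than divided by 0.85 (minor)

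*Protocol article*

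**What the plan says.** The protocol article, Sample size {14}, sets out the target in three steps. First, "The sample size is estimated with an alpha of 0.05 and a target power of 0.80". Second, the calculation "results in a required sample size of 134, with 67 participants in the intervention group and 67 participants in the waitlist control group". Third, citing two earlier intervention studies for the rate, it concludes: "a dropout rate of 15% is accounted for. The total required sample size is therefore 154". No inflation formula is given. The Methods paragraph of the abstract carries the total forward: effectiveness will be "investigated among a sample of 154 children". Allocation is 1:1 (Sequence generation {16a}).

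Three other sections bear on what the figure does:

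- Section {20c}, on non-adherence and missing data, puts all randomised participants, study dropouts included, into the main analysis and handles missing values by maximum likelihood.
- Trial status ends recruitment when the required sample size is reached, or in December 2023 at the latest.
- Interim analyses {21b} uses half of the required sample size after one year as the point at which interim analyses would be considered.

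**The concern.** The three printed numbers (134, 15% and 154) are presented as following from one another, but they do not. Adding 15% of the required number to itself is a different operation from enrolling enough children that the required number remains after 15% of them are lost. The first always gives a smaller total.

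What is at stake is whether the statement that 15% dropout is covered is true. The total also has a practical use: it is one of the two events that end recruitment, and it sets the one-year checkpoint. A number used in that way should match the basis given for it.

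**Working it through.** **Inputs, all from Sample size {14}:** required number 134 (67 per arm); dropout 15%; stated total 154; alpha 0.05; target power 0.80.

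**1. Reproducing the stated total.** n × (1 + d) = 134 × 1.15 = 154.1. Per arm, 67 × 1.15 = 77.05. Rounded to the nearest whole number, these give 77 per arm and 154 in total, exactly as printed. The protocol does not state this formula; it is inferred from the match.

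**2. Total needed for a 15% loss.** n / (1 − d) = 134 / 0.85 = 157.65, rounded up to 158. Per arm, 67 / 0.85 = 78.8, rounded up to 79. Check: 158 × 0.85 = 134.3, which is at least 134.

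**3. What 154 leaves at 15% loss.** 154 × 0.85 = 130.9, about 131 children with complete follow-up, so 134 − 131 = 3 short.

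**4. The loss that 154 does cover.** 1 − 134 / 154 = 0.130, or 13.0%.

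**5. Size of the gap in enrolment.** 158 − 154 = 4 children; 4 / 154 = 2.6%.

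**6. Effect on power, completers only.** The 134 cannot be recomputed. The article says that "the child-report means and standard deviations from previous sibling studies are used" but prints neither these values nor the expected changes. The check therefore assumes that 134 gives exactly 0.80 and scales the noncentrality by 130.9 / 134 = 0.977. For a two-sided test on 1 degree of freedom:

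- At 134: 1.960 + 0.842 = 2.802.
- At 130.9: 2.802 × √0.977 = 2.769.
- Power: Φ(2.769 − 1.960) = Φ(0.809) = 0.791.

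The article describes the hypothesis only as an interaction effect, so the degrees of freedom are not fixed by the text. The same scaling with a noncentral chi-square gives:

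| Degrees of freedom | Power at 134 (assumed) | Power at 130.9 |
|---|---|---|
| 1 | 0.80 | 0.791 |
| 2 | 0.80 | 0.790 |
| 4 | 0.80 | 0.789 |

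Once power is fixed at 0.80 for 134, the assumed correlations cancel. Only the ratio of sample sizes and the degrees of freedom matter, so about 0.79 holds across this range.

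**The case against.** The strongest reply is that the main analysis does not discard dropouts. Under section {20c} every randomised child enters it, and maximum likelihood uses whatever was observed. Families learn their allocation after the pre-test, so a child who leaves will normally have a T0 record, and one who leaves after T1 contributes T1 as well. This stands, and it limits the point to children with complete follow-up. It narrows the gap without closing it: a T0 record alone says little about the group-by-time contrast, and the full expected change is placed at T2, the last visit. Nor does it justify 154. If partial data made an allowance unnecessary, 134 would be enough; if a 15% allowance is wanted, the total is 158.

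A second reply is that the calculation already has a margin, because a scale factor of 1.2 for variability was inserted to be conservative. If that factor multiplies the variance (an assumption) and the unscaled variance is the true one, the 1-df power at 131 would be Φ(2.802 × √(1.2 × 131/134) − 1.960) = Φ(1.074) ≈ 0.86. This does not correct the dropout sum, but it counts against any suggestion of material loss of power.

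Third, the 15% is itself borrowed from two other studies, and its uncertainty may well exceed the difference between 13% and 15%. That is fair, and it is a reason to treat the point as minor.

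A reader might infer that fewer than 134 children will be analysed, that the trial is underpowered, or that 154 alone decides when recruitment stops. The documents support none of these. All randomised children are analysed; the power figure of 0.79 is a completers-only value resting on the assumption in step 6; and recruitment also has a calendar limit.

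**Conclusion.** The point holds as a minor arithmetic error. The stated total is 134 increased by 15%, and nothing elsewhere in the article makes it consistent with a 15% dropout rate in the ordinary sense of a share of those enrolled. At that rate the trial would have about 131 children with complete follow-up, three fewer than the number said to be required.

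The power cost is about one percentage point at most, provided that only completers count and that 134 gives exactly 0.80. Partial data should make the real cost smaller. The 134 itself is not challenged, and the validity of the trial is not in question.

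**What to change.** Either of two corrections makes the text consistent.

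- **Keep 154.** In Sample size {14}, replace the 15% statement with one saying that 154 allows for about 13% dropout, and that at 15% about 131 children would complete, with roughly 0.79 completers-only power if 134 gives 0.80. The abstract needs no change, because it gives only the sample of 154 and mentions neither dropout nor power. Cost: one sentence, no extra families.
- **Keep the 15% allowance.** Restate the total as 134 / 0.85 = 158 (79 per arm) in both Sample size {14} and the abstract, including the matching count of siblings and parents. Cost: the edits plus four more families, two per arm.

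The first is the cheaper and is sufficient. Whichever is chosen, printing the inflation formula beside the figure would let a reader check it.
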